### Participants

#### Patient Recruitment

The recruitment strategy primarily includes the use of posters, community sensitization, online promotion, and screening of patients from the respiratory outpatient department and those previously hospitalized.

We specifically targeted GOLD stage II-III patients for this study. This group gives us the best of both worlds: they have clear respiratory muscle dysfunction to detect mechanistic changes, yet are still able to safely perform the full Liuzijue protocol. We excluded stage I patients because they often lack measurable weakness, making improvement hard to detect—essentially a floor effect. Stage IV patients were excluded due to higher exacerbation risk and poor tolerance to exercise. We recognize this obviously limits generalizability to the broader COPD population. However, stage II-III is the largest and most clinically relevant subgroup in need of rehabilitation, and showing efficacy here is a logical first step before moving to more severe stages.

Before enrollment, participants will be provided with detailed information about this trial, including the research objectives, group allocation methods, intervention period, potential benefits, and possible risks. All participants must sign an informed consent form before the start of this trial to confirm their voluntary participation. Baseline assessments will then be conducted by the research team. All personal information will be anonymized and treated with strict confidentiality. It will be stored at the hospital and used exclusively for research purposes. Participants have the right to withdraw from this study at any time, and all cases of withdrawal and the corresponding reasons will be accurately documented by the research team.

#### Diagnostic Criteria

Based on the diagnostic criteria for COPD outlined in the 2023 GOLD guidelines [35] and *Chronic Obstructive Pulmonary Disease: Diagnosis and Management* [36], patients presenting with the following clinical manifestations can be diagnosed with COPD: (1) patients presenting with chronic cough, sputum production, dyspnea, wheezing, or chest tightness; (2) pulmonary function tests (PFTs) performed after inhalation of a bronchodilator showed a forced expiratory volume in one second (FEV₁) <80% of the predicted value and an FEV₁/forced vital capacity (FVC) <70%, indicating persistent airflow limitation despite medication; and (3) according to the GOLD guidelines, COPD being classified into four severity stages: I, II, III, and IV, based on the degree of airflow limitation and symptom severity.

#### Inclusion and Exclusion Criteria

Participants will be screened according to the predefined eligibility criteria before enrollment. Detailed inclusion and exclusion criteria are presented in Textbox 1.

Textbox 1.Inclusion and exclusion criteria for participant eligibility.Inclusion criteriaDiagnosed with stage II moderate chronic obstructive pulmonary disease (COPD) and stage III severe COPD.Maintained a stable condition for at least 12 weeks before randomization, with symptoms of cough, sputum production, and dyspnea remaining stable or mild, and no acute exacerbations occurring during this period.No gender restrictions; aged between 40 and 80 years.Participants who are willing to participate in this trial, can cooperate actively, and demonstrate good compliance.Patients who have not engaged in any form of regular traditional Chinese health-preserving exercises—defined as at least 30 minutes per session, twice daily, five times per week—during the six months before this trial.Exclusion criteriaPatients younger than 40 years or older than 80 years.Patients diagnosed with COPD who are experiencing an acute exacerbation requiring hospitalization or targeted pharmacological treatment.Patients who have participated in any structured pulmonary rehabilitation program, regular exercise training, or traditional Chinese health exercise programs within the 12 months before screening.Patients with COPD complicated by other respiratory diseases, such as asthma, pulmonary infections, tuberculosis, bronchiectasis, or lung cancer, who are deemed unsuitable for rehabilitation exercises.Patients with COPD complicated by severe diseases in other major systems, including cardiovascular, cerebrovascular, hematologic, hepatic, renal, digestive, endocrine, or nervous systems.Patients unable to cooperate with treatment and assessments due to conditions such as mental disorders or impaired consciousness.Participants concurrently enrolled in other clinical intervention or drug trials.Patients with musculoskeletal disorders or open injuries that preclude limb muscle strength assessment.

### Randomization and Blinding

SPSS (version 27.0; IBM) will be used to generate a random number list. A block randomization algorithm will assign a unique random number to each participant, and this information will be kept strictly confidential. All random numbers will be sealed in opaque envelopes, and group allocation will be performed using the envelope method. After completing baseline assessments, trained researchers will randomly select envelopes to assign participants to either the control group or the Liuzijue group according to the numbers contained therein.

Given that this trial involves physical intervention, it is difficult to blind the participants. Therefore, independent outcome assessors who are not involved in participant recruitment, intervention delivery, or group allocation will be used. All outcome assessments will be conducted by these blinded assessors according to standardized procedures. In addition, data analysts will also be blinded to group allocation in order to minimize bias and enhance the reliability of the results.

If it becomes necessary to unblind the outcome assessors or data analysts, the reasons must be documented and reported in detail. During data analysis, appropriate statistical methods will be applied to control potential bias.

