## Methods

### Research Design

This study is a randomized controlled clinical trial using a parallel design and evaluator blinding to investigate the effects of Liuzijue on respiratory muscle function in patients with stable COPD. Participants will be recruited from Shanghai Changhai Hospital. All patients will be in a stable phase, either receiving outpatient treatment or following hospitalization. A total of 76 clinically stable patients with COPD will be enrolled in this trial. Before the start of the intervention, respiratory physicians will perform diagnostic assessments to confirm eligibility. Eligible participants will subsequently meet with the research team to receive comprehensive information about this study’s objectives and procedures, and will be given the opportunity to ask questions. Subsequently, participants will sign the informed consent form and will then be randomly assigned to either the control group or the Liuzijue group in a 1:1 ratio.

This trial is conducted in accordance with the 2023 GOLD recommendations [35] and adheres to the diagnostic and evaluation criteria described in *Chronic Obstructive Pulmonary Disease: Diagnosis and Management* [36]. The current trial protocol has been approved (CHEC2025-149) by the Shanghai Changhai Hospital Medical Ethics Committee and has been registered with the Chinese Clinical Trial Registry (ChiCTR2500107043).

The total duration of this study is 9 months. The flowchart of this trial’s design is shown in Figure 1, and the details of patient recruitment, group allocation, interventions, and outcome measures are summarized in Table 1.

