### Sample Size Calculation

The sample size calculation for this study is performed using SPSS (version 27.0) and was based on the primary outcome of the 6-minute walk test (6MWT). According to evidence from previously published randomized controlled trials and systematic reviews in patients with COPD, the minimal clinically important difference (MCID) for 6MWT is approximately 54 m, and the baseline SD is generally reported to range between 70 and 90 m. To ensure a conservative and methodologically robust estimation, an SD of 80 m will be adopted for the present study [37,38].

A two-sided significance level of *α*=.05 and a type II error rate of *β*=.20 (80% power) were specified. Based on an MCID of 54 m, the required sample size is calculated using the following formula: $n=\frac{{\left(Z_{\frac{\alpha }{2}}+Z_{\beta }\right)}^{2}\times 2\times {SD}^{2}}{{MCID}^{2}}$. This yields a minimum sample size of 32 participants per group, for a total of 64 participants across both groups. Accounting for an anticipated dropout rate of 15%, the final required sample size is adjusted to 76 participants, with 38 participants allocated to each group.

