## Results

This trial is supported by the Traditional Chinese Medicine Research Project of the Shanghai Municipal Commission of Health (No. 2024QN094), which was awarded in May 2024. Participant recruitment commenced in August 2025. As of submission of this manuscript, 23 participants had been enrolled, including 15 participants in the control group and 8 participants in the Liuzijue group. Data collection is expected to be completed by late 2026, followed by statistical analysis in early 2027. This study’s protocol (version 1.1) commenced participant recruitment on August 1, 2025. Recruitment is expected to be completed by September 2026, followed by data collection through December 2026. Data analysis is planned for January 2027. The final trial results are anticipated to be published in spring 2027.

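### Envelopes from a blocked 1:1 list are picked at random, so the list order is not used: balance over time and an auditable allocation order are lost, and the 15:8 split suggests blocking is not operating

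*Protocol article*

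**What the plan says.** Under Research Design, the protocol article has participants "randomly assigned to either the control group or the Liuzijue group in a 1:1 ratio", and it names one recruiting hospital: "Participants will be recruited from Shanghai Changhai Hospital".

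Randomization and Blinding then sets out three steps. The list is blocked: "A block randomization algorithm will assign a unique random number to each participant". Concealment is by envelope: "All random numbers will be sealed in opaque envelopes, and group allocation will be performed using the envelope method". The envelopes are used after baseline assessment, when "trained researchers will randomly select envelopes to assign participants to either the control group or the Liuzijue group according to the numbers contained therein". The section does not tie envelopes to a numbered order. The article gives no block size and names no stratification factor.

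Sample Size Calculation sets the target: "the final required sample size is adjusted to 76 participants, with 38 participants allocated to each group". Results reports progress at submission: "23 participants had been enrolled, including 15 participants in the control group and 8 participants in the Liuzijue group". The Abstract gives the same two counts. Neither place explains the difference between the arms.

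**The concern.** A permuted-block list balances the arms because of its order: each run of assignments the length of one block contains equal numbers of both arms. If the person allocating picks any envelope from the set, that order plays no part. The section therefore names one method (blocking) and prescribes a step that cancels it. This is a stated rule, so it cannot be put down to detail that an article leaves to the full protocol.

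Two things are at stake. The first is balance during recruitment, and at the end if the trial stops short of its target. The second is the audit trail. When no envelope belongs to the next participant, nobody can later confirm against the list that the envelope used was the one due. That matters more here because participants cannot be blinded, and because walking distance and questionnaire scores depend on effort and self-report. The section keeps outcome assessors out of recruitment and allocation, but sets no such separation for the researchers who pick the envelopes.

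**Working it through.** **Inputs.** Allocation 1:1, one hospital (Research Design). Blocked list, block size and strata not stated (Randomization and Blinding). Enrolled so far: 15 control and 8 Liuzijue (Results). Target: 76, 38 per arm (Sample Size Calculation). Assumption: 15 and 8 are the complete counts of participants allocated.

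**Observed gap.** 15 + 8 = 23 and 15 − 8 = 7.

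**One unstratified list used in order.** With 1:1 blocks of size B, completed blocks contribute no imbalance, and an incomplete block contributes at most B/2.

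- Blocks of 4, 6, 8, 10 and 12 allow a gap of at most 2, 3, 4, 5 and 6 at any time. A mix of sizes up to 12 is also limited to 6. The observed 7 lies outside all of these.
- At exactly 23 participants, fixed blocks are tighter still, because only the remainder of 23 divided by B can be unbalanced. For B = 12 the remainder is 11, split 6:5 at worst, a gap of 1. For B = 2, 4, 6 or 8 the maximum is also 1. For B = 10 the remainder is 3, so the maximum is 3. For B = 14 the remainder is 9, split 7:2 at worst, so the maximum is 5.
- The smallest fixed block that allows 15:8 is 16. The remainder is 7, and all seven must be control: C(8,7) / C(16,7) = 8 / 11,440 = 0.0007 (0.0014 for a gap of 7 or more in either direction).
- Fixed blocks of 18 to 28 rule it out again. At 30 its probability is 0.003.
- With mixed sizes, at least one block of 14 or more is needed.

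**Envelopes drawn at random from a 38:38 pool.** The number of controls among 23 is hypergeometric: P(X = x) = C(38,x) C(38,23−x) / C(76,23). P(X = 15) = 0.044. P(X ≥ 15 or X ≤ 8) = 0.133.

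**Simple 1:1 randomisation, for comparison.** Binomial(23, 0.5): P(X ≥ 15 or X ≤ 8) = 0.210.

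**What remains.** 76 − 23 = 53 allocations. If the pool was 38:38, the unused envelopes are 38 − 15 = 23 control and 38 − 8 = 30 Liuzijue, so the next draw is Liuzijue with probability 30/53 = 0.57. If a fresh 1:1 list is used for the 53 instead, adding 26 or 27 to each arm ends at 41–42 control and 34–35 Liuzijue.

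**The case against.** The strongest objection concerns how much the 15:8 split can carry. Three parts of it stand.

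- A reader might infer that the split is impossible under blocking. The documents do not support that without conditions. They state neither block size nor strata, which an article may leave to the full protocol. Two strata with blocks of 8 to 12, three with blocks of 6, or four with blocks of 4 could give a gap of 7. The counts are also described as enrolled, not randomised. The Liuzijue Group section gives that arm three training sessions before the intervention starts, so its count could lag if enrolled means started.
- A reader might infer that allocation has been steered. The documents do not support that either. Honest random drawing, which is what the text prescribes, gives a gap this large about 13% of the time. No text permits an envelope to be redrawn or discarded.
- A reader might infer that the final 1:1 ratio is lost. It is not, if 38:38 envelopes are prepared and all are used. At one hospital recruiting from August 2025 to September 2026, imbalance over calendar time is a modest concern.

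Real safeguards exist as well: the envelopes are opaque and sealed, the list is confidential, and eligibility, consent and baseline assessment come before allocation. The 0.57 chance for the next draw is only mildly predictable, whereas late positions in small blocks used in order can be fully predictable.

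None of this removes the conflict between a blocked list and unordered picking, or supplies the missing link between participant and envelope.

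**Conclusion.** The defect in the written rule is clear and does not depend on the 15:8 figure. A blocked list is generated and its order is then not used. What is lost is balance within blocks over time, final balance if recruitment stops before all envelopes are used, and an allocation order that can be audited. Concealment is weakened despite the sealed opaque envelopes, not abolished.

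The split is supporting evidence of limited weight. On a single unstratified list used in order, and with 15 and 8 as complete allocation counts, a gap of 7 exceeds the limit of 6 for blocks of 12 or fewer. Among fixed blocks it first becomes possible at size 16, with probability 0.0007. Under random drawing from a 38:38 pool it is unremarkable, at 0.13. It therefore suggests that blocking is not operating, and it says nothing about manipulation.

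The rule needs correcting now: 53 of the 76 allocations were still to be made when the article was submitted, and no analysis can restore the order of allocation afterwards.

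**What to change.** 1. Replace the picking rule. Number the envelopes in list order, write the participant ID and date on the envelope before opening it, and open strictly in sequence. Existing staff not involved in recruitment or assessment should do this.
2. State how the remaining 53 allocations are listed. One option is a new blocked 1:1 list, accepting about 41–42 control to 34–35 Liuzijue at the end. The other is to put the unused envelopes (23 control and 30 Liuzijue, if the pool was 38:38) into a newly generated, concealed random order.
3. Check the first 23 allocations against the envelope contents and the list. Use out of list order is not in itself a protocol deviation, because the current text prescribes random picking. The check should establish that each participant's arm matches an envelope and that every opened envelope is accounted for.
4. State whether 15 and 8 are randomised counts and whether strata were used, and report the change of procedure. An analysis by allocation period is optional; with 23 against 53 participants it would be imprecise.

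The cost is a short amendment, a revised operating procedure and a check of 23 envelopes. No patients, visits or measurements are added.

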### Sample Size Calculation

The sample size calculation for this study is performed using SPSS (version 27.0) and was based on the primary outcome of the 6-minute walk test (6MWT). According to evidence from previously published randomized controlled trials and systematic reviews in patients with COPD, the minimal clinically important difference (MCID) for 6MWT is approximately 54 m, and the baseline SD is generally reported to range between 70 and 90 m. To ensure a conservative and methodologically robust estimation, an SD of 80 m will be adopted for the present study [37,38].

A two-sided significance level of *α*=.05 and a type II error rate of *β*=.20 (80% power) were specified. Based on an MCID of 54 m, the required sample size is calculated using the following formula: $n=\frac{{\left(Z_{\frac{\alpha }{2}}+Z_{\beta }\right)}^{2}\times 2\times {SD}^{2}}{{MCID}^{2}}$. This yields a minimum sample size of 32 participants per group, for a total of 64 participants across both groups. Accounting for an anticipated dropout rate of 15%, the final required sample size is adjusted to 76 participants, with 38 participants allocated to each group.

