#### 6MWT

6MWT is a widely used method for evaluating exercise capacity in patients with respiratory disorders and for assessing the efficacy of clinical interventions. Previous studies [48,49] have demonstrated that the 6MWT serves as a valid and reliable measure of functional capacity and health-related quality of life in patients with COPD, while also providing an indicator of disease severity. Based on previous findings [37,38], the MCID for 6MWT ranges from 30 to 54 m, and the baseline SD is between 70 and 90 m. This study will use a 6MWT data acquisition system in combination with a dynamic vital signs monitor, CB200 (Contec), for testing. Participants will be instructed to walk back and forth along a 30-meter flat corridor at their maximum tolerable speed for six minutes. Distance markers will be placed every 5 meters to aid measurement. The recording device will capture the total walking distance as well as heart rate and oxygen saturation before and after the test. The 6MWT outcome will serve as a primary indicator of intervention efficacy, assessed in week 0 and week 13.

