### Statistical Analysis

Statistical analyses will be executed using SPSS (version 27.0), adhering to a two-sided significance threshold of *P*<.05 while reporting effect sizes and 95% CIs where appropriate. Baseline characteristics will be summarized solely through descriptive statistics without formal hypothesis testing, with continuous variables first evaluated for normality and homogeneity of variance to determine their presentation as either mean with SD or median with IQR.

Under an intention-to-treat framework encompassing all randomized participants, missing data patterns will be evaluated and addressed via multiple imputations, the robustness of which will be subsequently verified through sensitivity analyses including per-protocol and complete-case approaches. Primary outcomes will be modeled using linear mixed-effects specifications that will incorporate group, time, and their interaction as fixed effects alongside participant-level random intercepts to account for the repeated-measures design.

For continuous secondary outcomes, analysis of covariance adjusted for baseline values will be used where appropriate, whereas other continuous and categorical variables—the latter summarized as frequencies and percentages—will be scrutinized using parametric, nonparametric, chi-square, or Fisher exact tests depending on data distribution, with false discovery rate adjustments applied throughout to mitigate type I error inflation from multiple comparisons.

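### The 6MWT sample size rests on a single-occasion baseline SD of 80 m, while the primary model most naturally tests change, so the stated 80% power is not established for the planned test

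*Protocol article*

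**What the plan says.** The Sample Size Calculation section gives the test level as "A two-sided significance level of *α*=.05" and a "type II error rate of *β*=.20 (80% power) were specified". The target difference is 54 m: "the minimal clinically important difference (MCID) for 6MWT is approximately 54 m". On variability it reports that "the baseline SD is generally reported to range between 70 and 90 m" and then states: "To ensure a conservative and methodologically robust estimation, an SD of 80 m will be adopted for the present study". These go into the standard two-sample formula for means, with a stated result of 32 per group (64 in total), raised to 76 for 15% dropout.

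The 6MWT section repeats the label, saying that "the baseline SD is between 70 and 90 m", and schedules the test at week 0 and week 13.

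The Statistical Analysis section models the primary outcomes by "linear mixed-effects specifications that will incorporate group, time, and their interaction as fixed effects alongside participant-level random intercepts". It does not say which coefficient or contrast is the test of efficacy. No correlation between the two visits and no SD of change appears anywhere in the article.

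**The concern.** A baseline SD describes how far patients differ from one another on one occasion. Put into a two-sample formula, it gives the power to compare the groups' 6MWT values on one occasion. A model with group, time and their interaction over two visits is normally read through its interaction term, which compares the groups on mean change. Change has a different SD, and how different depends on a correlation that the article does not state.

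This matters because the Discussion says that the sample size was based on the 6MWT alone, since data on surface electromyography were too limited. The 80% is therefore the trial's only power statement. If it does not describe the test that will be run, readers cannot tell what the trial was designed to detect. The description of 80 m as conservative also has no support for that test.

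**Working it through.** **Inputs from the article.** Two-sided α = 0.05; power 80%; difference 54 m; single-occasion SD 80 m; stated n = 32 per group; 15% dropout; visits at weeks 0 and 13.

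**Assumed inputs.** The correlation r is not given, so it is varied from 0.3 to 0.8. The SD is taken as 80 m at both visits and in both groups, and data are complete for the evaluable participants.

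**Step 1: the plan's own figure.** The printed formula is n = 2 × SD² × (z for α/2 + z for β)² / MCID². With z values of 1.960 and 0.842, the squared sum is 7.849. Then n = 2 × 6400 × 7.849 / 2916 = 34.45, which rounds up to 35 per group (70 in total). The stated 32 (64 in total) does not reproduce. It would need an SD of about 77 m or a difference of about 56 m. At 32 per group with an SD of 80 m, power is 77.0% by the normal approximation and 75.7% by the t-test. The dropout step is right for its input: 64 / 0.85 = 75.3, so 76.

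**Step 2: the SD that governs change.** With two visits, complete data and a random intercept, the interaction estimate equals the between-group difference in mean change. The variance of a within-person change is 80² + 80² − 2r × 80², so SD of change = 80 × sqrt(2(1 − r)). This equals 80 m only at r = 0.5. It is larger below that and smaller above it.

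**Step 3: power for change.** Two-sided 0.05 t-test, difference 54 m. The last column puts the SD of change into the plan's own formula and rounds up.

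| Assumed r | SD of change (m) | Power, 32 per group | Power, 35 per group | Formula n per group for 80% |
|---|---|---|---|---|
| 0.3 | 94.7 | 61% | 65% | 49 |
| 0.4 | 87.6 | 68% | 72% | 42 |
| 0.5 | 80.0 | 76% | 79.5% | 35 |
| 0.6 | 71.6 | 84% | 87.5% | 28 |
| 0.7 | 62.0 | 93% | 95% | 21 |
| 0.8 | 50.6 | 99% | 99% | 14 |

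**Step 4: separating the two issues.** In the r = 0.5 row the two SDs coincide, so the shortfall at 32 per group (76%) is entirely the arithmetic slip of Step 1. The 35-per-group column shows the choice of SD on its own: power crosses 80% at r of about 0.5. At 32 per group the crossing moves up to about 0.55, and the extra 0.05 comes from the arithmetic.

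**Step 5: a baseline-adjusted analysis, for comparison.** Its residual SD is 80 × sqrt(1 − r²), which never exceeds 80 m. At 32 per group the t-test power is 80%, 87% and 96% at r = 0.3, 0.5 and 0.7. So 80 m is a safe upper value for the baseline-adjusted method that the article gives to continuous secondary outcomes, but not for a comparison of change.

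**The case against.** Four points can fairly be made in the plan's defence.

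First, the Statistical Analysis section does not name the tested coefficient. A between-group contrast at week 13 can be taken from the same model, and with complete data the single-occasion SD would govern it. This stands as far as it goes: that change is the target is an inference. It is the natural one, because the Discussion describes the aim as evaluating changes before and after the intervention, with the 6MWT as primary. If a week-13 contrast is meant, the text should say so.

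Second, the direction is unknown. Above r = 0.5 the single-occasion SD is the cautious choice and power is understated. This stands in full. A reader might infer from the low-r rows that the trial is underpowered; the documents give no r and do not support that.

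Third, a condensed article may leave an assumed correlation to the full protocol or analysis plan. That is true of a bare omission. Here, though, the article prints the formula, the SD, its label, the claim that it is conservative, and the primary model, and these printed items do not fit together as they stand.

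Fourth, a reader might infer that a null 6MWT result could not be interpreted. That goes too far. Such a result would be read from its estimate and confidence interval, and the article commits to effect sizes and 95% CIs.

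**Conclusion.** The concern holds in a limited form. The 80% power is computed from a single-occasion SD and is not established for the comparison of mean change that the primary model most naturally makes. With 54 m, a single-occasion SD of 80 m and 32 evaluable per group, power for change lies between 61% and 99% as r goes from 0.3 to 0.8. At 35 per group the range is 65% to 99%. The word conservative is justified for this contrast only if r is above 0.5.

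A reader might take the 80% to be correct at least for a simple comparison of 6MWT values on one occasion. It is not: the printed inputs need 35 per group, and 32 gives about 76–77%. That is a separate arithmetic error, and correcting it leaves the question of the SD open.

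What is shown is a power figure that needs restating and an unsupported description of the SD. A power shortfall caused by the choice of SD is not shown. The conclusion rests on reading the interaction as the test of efficacy and on equal SDs at the two visits.

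**What to change.** In the Sample Size Calculation section:

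- Name the 6MWT contrast to be tested (difference in mean change, or week-13 difference), and make the Statistical Analysis section agree.
- State the assumed correlation between weeks 0 and 13, or the SD of change, with its source.
- Restate the power for 64 evaluable participants over a plausible range of r, such as 0.4 to 0.8, using 80 × sqrt(2(1 − r)). If the primary analysis is baseline-adjusted, use 80 × sqrt(1 − r²) instead.
- Drop the word conservative unless it holds for the contrast named.
- Separately, correct 32 to the 35 per group that the printed inputs give, or print the inputs that yield 32. If the target stays at 64 evaluable, report the power that this number actually gives.

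The cost is a few sentences and a small table. This point requires no extra patients and no new data, and the sample size need not change. The downside is that a single 80% becomes a range, which may look less favourable at low r.

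### The printed sample-size formula gives 35 per group, not 32; by the same calculation, 64 evaluable participants give about 77% power for 54 m, not 80%

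*Protocol article*

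**What the plan says.** The Sample Size Calculation section sizes the trial on the 6MWT alone. It sets two-sided alpha at .05, power at 80% and the difference at 54 m. On the SD it says: "To ensure a conservative and methodologically robust estimation, an SD of 80 m will be adopted for the present study". It prints the usual normal-approximation formula for two means, n = (Z for alpha/2 + Z for beta)² × 2 × SD² / MCID², and states the result: "This yields a minimum sample size of 32 participants per group, for a total of 64 participants across both groups". A 15% dropout allowance raises 64 to 76, or 38 per group, and the Research Design section takes this up as the enrolment target: "A total of 76 clinically stable patients with COPD will be enrolled in this trial".

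The 6MWT section, citing the same two references, gives ranges for both inputs: "the MCID for 6MWT ranges from 30 to 54 m, and the baseline SD is between 70 and 90 m".

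The Statistical Analysis section plans a linear mixed model for the primary outcomes, with group, time, their interaction and a random intercept per participant. It reserves baseline-adjusted ANCOVA for continuous secondary outcomes.

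**The concern.** The formula and every input are printed, so the result can be checked directly, and it does not come out at 32. The enrolment target is built on that number, so the error carries into the 76. The other coprimary outcome, surface electromyography, was not sized (the Discussion says the published data were too limited), so the 80% figure is the trial's only quantitative justification of its size.

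The wording adds to the problem. A reader told that the estimate is conservative will assume some slack in it, whereas the SD is mid-range and the arithmetic errs towards fewer participants. A 6MWT result that misses significance could then be given more weight as evidence of no effect than the calculation supports.

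**Working it through.** **Inputs.** From Sample Size Calculation: two-sided alpha .05 (z = 1.960), power 80% (z = 0.8416), SD 80 m, difference 54 m, dropout 15%. From Research Design: 1:1 allocation. From 6MWT: difference range 30-54 m, SD range 70-90 m.

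**Reproducing the stated figure.**
- n = (1.960 + 0.8416)² × 2 × 80² / 54² = 34.45, so 35 per group and 70 in total.
- With z values rounded to 1.96 and 0.84: 34.41, again 35.
- Variants: one-sided alpha gives 28; a t-based calculation gives 36. Neither gives 32.
- To reach 32, the formula needs an SD of about 77 m (SD 77 gives 31.9) or a difference of about 56 m. The protocol states neither.

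**Dropout step.**
- From the stated figures: 32/0.85 = 37.6, so 38; 64/0.85 = 75.3, so 76. This step is done correctly.
- From the correct figure: 35/0.85 = 41.2, so 42 per group (84 in total).

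**Power at the planned size.** Power = Φ(difference / (SD × √(2/n)) − 1.96).
- n = 32, SD 80, 54 m: 54 / (80 × 0.25) = 2.70; Φ(0.74) = 77.0%. Noncentral t: 75.7%.
- n = 38 (no dropout): 83.7% by the formula, 82.7% by t.
- n = 35 (38 less about 8%): 80.6% by the formula, 79.5% by t.

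**Sensitivity over the protocol's own ranges, n = 32 per group (formula / t-test).**

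| Difference | SD 70 m | SD 80 m | SD 90 m |
|---|---|---|---|
| 54 m | 87.0% / 85.9% | 77.0% / 75.7% | 67.0% / 65.6% |
| 30 m | 40.3% / 39.3% | 32.3% / 31.5% | 26.6% / 25.9% |

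**What baseline data could change.** The protocol states no baseline-to-week-13 correlation (rho), so any value is an assumption. Equal SDs at both visits and complete data are also assumed.
- ANCOVA: the required n is (1 − rho²) × 34.45. For this to be at most 32, rho must be at least √(1 − 32/34.45) = 0.27.
- Planned mixed model with a free group term and two visits: the group-by-time contrast is a comparison of changes, with variance 2 × SD² × (1 − rho). The required n is 2(1 − rho) × 34.45. For this to be at most 32, rho must be at least 1 − 32/68.9 = 0.54.
- Power of that mixed-model contrast at 32 per group, by the normal formula: about 63% at rho 0.3, 77% at rho 0.5 and 94% at rho 0.7.

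**The case against.** The strongest reply is that 77% is the power of a test the trial does not plan to run. The formula describes an unadjusted comparison of two means, while the stated primary analysis is a group-by-time mixed model whose power depends on an unstated correlation. This stands. A reader might infer that the trial is underpowered, but the protocol does not support that: actual power under the planned model could lie on either side of 80%. What is shown wrong is the stated calculation. The reply does not rescue the 32 either, since the printed formula contains no correlation.

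The shortfall is also small and depends on dropout: 3 per group before inflation, and 3-4 points of power only if the full 15% is lost. By the formula, 80% still holds if 35 per group remain. That is correct, but the protocol itself plans for 15%.

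A reader might also count the choice of 54 m as part of the error. It is not. The value lies within the protocol's cited range, and choosing it is a design decision. The word conservative is attached to the SD and the estimation, not to 54 m. The low power at 30 m is therefore useful context and does not measure this mistake.

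Finally, the plan to report effect sizes with 95% CIs where appropriate limits the risk that a null result is over-read. It does not correct the stated number.

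**Conclusion.** Wrong as written. With the protocol's own formula and inputs, the requirement is 35 per group (70; 84 after 15% dropout), not 32 (64; 76). By that calculation, 64 evaluable participants give 77.0% power (75.7% by t-test) for 54 m at SD 80 m. This rests on an unadjusted comparison, equal SDs and the full planned dropout; with no dropout the figure is about 83-84%.

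Calling the SD of 80 m conservative is not supported, because it is the midpoint of the range quoted in the sentence before. The error is modest, and it invalidates no test or procedure. It is nevertheless a false figure on which the enrolment target rests.

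**What to change.** In Sample Size Calculation, change 32 per group and 64 in total to 35 and 70, and state that 15% dropout takes this to 42 per group (84). Delete the word conservative for the SD of 80 m, give power at 90 m as well (about 66-67%), and note that 54 m is the upper end of the range in the 6MWT section. Then choose one of these:

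- **Keep 76 and restate the power** as about 76-77% for 54 m at SD 80 m with 15% dropout. This costs wording and one less favourable figure; no extra participants.
- **Keep 76 and the 80% claim.** Prespecify in Statistical Analysis a baseline-adjusted (ANCOVA) primary analysis of the 6MWT, and state and justify the assumed correlation (at least about 0.27 by the normal formula; somewhat higher if t-based). This needs no extra participants but changes the primary model, so it should be a dated amendment made before outcome data are examined. If the mixed model with a free group term stays, the correlation to justify is about 0.54.
- **Raise enrolment to 84.** This costs 8 more participants. At submission 23 were enrolled and recruitment was expected to run to September 2026.
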